**Single active ingredient**												
	active-3	Medium		Survival	0.0079		30	0.5000		6.4054		1.8438
	active-5	Low		Survival	0.0081		31	0.4366		5.5934		1.6364
	active-1	Low		Survival	0.0013		5	0.4166		5.3378		1.5804
	active-4	High		Survival	0.0013		5	0.4166		5.3378		1.5804
	active-2	Low		Survival	0.0021		7	0.4000		5.1243		1.5365
**Combination of active ingredients**												
	active-3 and active-2	Medium, low		Survival	0.0021		7	0.8888		11.3873		8.2974
	active-5 and active-1	Low, low		Survival	0.0015		6	0.7500		9.6081		3.6877
	active-4 and active-2	High, low		Survival	0.0013		5	0.7142		9.1505		3.2267

In addition, it is possible to filter by age, gender, or patient group, as well as search for relationships between them and their survival. Similarly, combinations of active ingredients can be sought that lead to increased survival (Table 1).

### Statistical Analysis

To achieve the primary objective, several exploratory analyses will be performed. These will look for an association between the use of the different drugs available in the database (the exposure variable) and patient survival (the outcome variable). The exposure variable will be treated both dichotomously (exposed or not exposed) and quantitatively. The time exposed to the drug, the average monthly dose, the maximum dose, or the cumulative dose per unit of time will be considered. Specific analyses will be carried out on the effect of 2 or more drugs that have been shown to influence survival when they have been consumed, either simultaneously or sequentially, within the time unit being analyzed. The outcome variable is survival during the observation period. Patients who are censored, for whom no death is recorded during the follow-up time, are considered alive at the end of the period.

In addition to the machine-learning techniques described above, the association between exposure and outcome will be investigated using 2 different approaches. The exposure odds for each drug will be calculated, and this exposure will be compared between patients considered alive at 5 years and those who have died using odds ratios (exposure odds ratio). The group of nonsurvivors will be selected with different time criteria in a sensitivity analysis: deceased in the 1st, 2nd, or 3rd year after diagnosis. Second, the survival time of participants exposed and unexposed to each drug available in the database (individual agents, ATC5 codes) or to each family of agents (ATC4 codes) will be compared.

To avoid bias due to a lack of randomization, in both approaches, matching will be carried out between the groups with respect to confounding variables. In addition, if residual confounding is suspected or an imbalance between groups remains after matching, adjustments for age, sex, and diagnostic groups will be performed. A Cox regression model will be constructed to estimate the effect of the evaluated drug. The hazard ratio (HR) and its 95% CI will be reported. Hazard proportionality will be assessed graphically by Schoenfeld residuals.

As a secondary objective, we plan to analyze the relationship between the presence of various nonneoplastic diseases and the survival of patients with cancer. To do this, we will compare the survival of patients with a specific disease to those who do not have it, adjusting multivariate models for age, gender, other conditions that may impact survival, and medications that have previously been shown to modify survival in previous analyses.

All analyses conducted in the cohort of patients with cancer will be replicated in a control patient group matched by age to the patients with cancer (with expected lower mortality) and in another group of older patients, where each control will be 10 years older than their cancer counterpart (with expected higher mortality). The findings that are reproduced in these groups of the control cohort will be discarded, as they are considered the result of uncontrolled biases or general effects on survival, not related to the cancers under study.

To consider a result statistically significant, the P value will be set at P=.05. All analyses are considered exploratory and hence subject to confirmation in new studies; therefore, no correction techniques will be applied to the P values obtained. All statistical analyses will be performed using R statistical software (version 4.1.0 or higher; R Core Team).

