Hospital CMBD is a database in which diagnoses and procedures performed on hospitalized patients are recorded throughout the Spanish territory; all public hospitals and the majority of private hospitals (>95% hospital coverage) are included [14].Estació Clínica d'Atenció Primària (ECAP) is an electronic medical history program launched in 2001 and used by family doctors, pediatricians, and nurses from the Catalan Institute of Health (Institut Català de la Salut [ICS]) primary care centers when they visit patients; it includes all previous illnesses known to the primary care physician and records of the health care process in the outpatient setting, including assessments by health care personnel, diagnostic tests, and treatment, among others. The PADRIS program has only provided data since 2006, after which data are considered to be of good quality.The registry of causes of death is prepared by the INE using data from the Medical Certificate of Death or Statistical Bulletin of Death, Statistical Bulletin of Judicial Death, and Statistical Bulletin of Childbirth. It is prepared following the criteria established by the WHO (World Health Organization) in the International Classification of Diseases (ICD), which includes more than 12,000 diseases.Electronic prescription has been implemented in Catalonia progressively since 2010 and is currently deployed in 100% of primary care centers, pharmacies, and public hospitals in Catalonia. Prescribing and dispensing data will be obtained from the Comprehensive Health Information System of the Catalan Health Service (Servei Català de la Salut [CatSalut]), which is a computerized system used by the doctors of the national health system in Catalonia to prescribe financed pharmacological treatments to their patients and the pharmacies to dispense them; it contains information on the date of the prescription, the active ingredient, and dose, among other variables. Unfunded treatments can be prescribed using this tool but are often prescribed by other means (paper prescriptions).

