### Outcome Variables and Measurements

The primary end point is survival, calculated from the date of entry in the database until death or until 5 years of follow-up are reached. For patients in cohort 1, the earliest date of cancer diagnosis for which they have been selected to be part of the cohort will be considered the date of entry into the study (inclusion criterion).

As study variables, the following data will be collected from all patients:

List of diagnosed diseases (data source: CMBD and ICS ECAP diagnostic registry)Date of death (data source: INE cause of death registry)Cause of death (data source: INE cause of death registry)Pharmacological treatment (data source: Catalan electronic prescription), including all prescribed active ingredients, drug withdrawal dates from pharmacies, consumed doses, and prescribed regimen, during the entire follow-up periodSex (data source: Sistema Integral d'Informació de Salut)Date of birth (data source: Sistema Integral d'Informació de Salut)Basic health area (data source: Sistema Integral d'Informació de Salut)

For the patients included in the study with one of the cancers under study (cohort 1), the following variables will also be collected:

Type of cancer and presence of metastases (data source: CMBD and ICS ECAP diagnostic registry)Date of diagnosis for which the patient is included in the cohort (data source: CMBD and ICS ECAP diagnosis registry)Surgical treatment of the cancer (data source: CMBD)Date of surgical treatment (data source: CMBD)

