### Data Curation

The data used in this study will be obtained from different databases, which must be merged for the analysis. None of the databases will be sorted by patient but by other types of entries (drugs, diagnoses, procedures performed, etc); therefore, the same patient could appear multiple times in each of them. Thus, first, a date will be associated with each event, and the information in the databases will be sorted by patient, with each patient as an entry that appears only once.

The coding of diseases and therapeutic procedures has undergone changes during the years of collection in the cohort, transitioning from using International Classification of Diseases, Ninth Revision (ICD-9) coding to ICD-10 coding. Consequently, all the data with ICD-9 coding will have to be converted to ICD-10 using the conversion tables provided by the Government of Catalonia (Generalitat de Catalunya) on their website [15].

In the pharmacological dispensing database, the active principles will be collected through the Anatomical Therapeutic Chemical (ATC) Classification System, and the amount dispensed monthly will be determined using the number of defined daily doses (DDDs) [16]. DDDs change over the years and are not uniform for different active ingredients or for drugs that form different groups as defined by the ATC4 codes. Thus, when necessary, DDDs will be transformed into units of mass for each of the drugs using the tables provided by the WHO with the evolution of DDDs over time [17].

One of the databases managed includes patients with metastases of any origin. For these patients, their previous diagnoses will be traced, and all the codes for both the CMBD and the ECAP will be analyzed to search for cancer diagnoses before metastasis to determine the origin of the cancer.

Finally, a patient rejection process will be applied based on the consistency of dates between the different databases. Following this principle, all those patients who, having been included in the database, do not have electronic prescription records will be rejected. In addition, all patients without registration or enumeration in the death databases will be excluded. Finally, patients with inconsistent dates will be excluded, for example, with postdeath records in the CMBD, ECAP, or electronic prescription.

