## Discussion

The aim of this study is to identify drugs for commercial use for pathologies with an effect on the survival of patients with cancer. For the study, diseases that have high lethality (survival rate <20% at 5 years) will be selected because they are a priority in terms of the search for new therapies and because for these diseases, conventional treatment has had little impact on survival, which facilitates the observation of additional survival effects from other drugs. The diseases have also been selected for their high frequency, so that, despite the high lethality, the group of survivors at 5 years will be large enough to allow comparisons with the deceased group with sufficient statistical power.

Despite the good quality of the data used, this study is based on analyses of secondary data and, therefore, has certain limitations that, although hypotheses can be established, make it necessary for these hypotheses to be tested through trials that generate primary data.

First, we do not have all the variables that can act as confounding factors in patient survival. For example, we do not have data on the histology of the various tumors, which can impact survival. Especially important is also the absence of data on hospital treatment for cancer, which does not appear in any of the available databases. Due to this limitation, the study has been designed to investigate “long survivors” (5 or more years) because, for the diseases studied, there are no treatments that have been shown to extend survival to the fifth year. For this reason, it is not probable that hospital treatments act as a confounding factor (because they have no known association with the outcome studied: survival after 5 years).

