Second, patient registration in the databases does not coincide exactly with disease onset, resulting in a shortened estimated time to death. This limitation is greater in the CMBD than in the ECAP databases; therefore, one database will be complemented with the other to alleviate this limitation. However, this temporal bias has an established direction: registration in the databases always occurs after the diagnosis. This allows all cases to be classified correctly in the group of patients identified as long survivors because patients who lived 5 years since their inclusion in the database will have lived at least 5 years from disease diagnosis. However, there will be a classification error whereby some long survivors, for whom their data were entered late in the databases used, will fall within the comparison group (classified as “nonlong survivors”). This error will affect at most 20% of the comparison group because that is the maximum survival at 5 years estimated for the diseases under study. Therefore, the specificity of the classification will be at least 80%, and for some cancers, it will reach 95% (such as metastatic bladder cancer or metastatic stomach cancer). This classification error will bias the results toward the null hypothesis, not invalidating the differences ultimately found between groups, although it does detract from the power of the study. Given that the magnitude of the effect sought is very large, we do not believe that the decline in power due to classification bias prevents the observation of these differences.

Third, despite the shortening of the time frame of the data analysis for each patient to control for reverse causality and “immortal patient” biases, there may be a residual effect derived from these biases within the time frame not eliminated from the analysis; however, we expect this effect to be much smaller. In addition to the aforementioned biases, there may be information biases, mainly due to pathologies not registered in the database. We do not expect that these biases will significantly affect the main variables because cancer diagnoses are usually registered in the databases used as soon as they are known, the pharmacological registry includes drugs dispensed in pharmacies (not only prescribed), and registry mortality is very reliable.

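### Dose averaged over calendar time treats hospital days as days without drug, so the dose analyses can show a false dose-response where hospital time is related to prognosis

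*Protocol article*

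**What the plan says.** All references are to the Protocol article.

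- **Source of exposure.** Outcome Variables and Measurements lists "Pharmacological treatment (data source: Catalan electronic prescription), including all prescribed active ingredients, drug withdrawal dates from pharmacies, consumed doses, and prescribed regimen". Data Sources describes a system that doctors use to "prescribe financed pharmacological treatments to their patients and the pharmacies to dispense them".
- **Source of the amount.** Data Curation states that "the amount dispensed monthly will be determined using the number of defined daily doses (DDDs" in the dispensing database.
- **Dose measures.** In Statistical Analysis, besides time exposed, "the average monthly dose, the maximum dose, or the cumulative dose per unit of time will be considered". In Machine Learning, one set of association rules uses the average DDD over the patient's survival time, cut into three quantiles.
- **Hospital data.** Data Sources says "Hospital CMBD is a database in which diagnoses and procedures performed on hospitalized patients are recorded throughout the Spanish territory"; drugs given on the ward are not mentioned. The Discussion concedes the "absence of data on hospital treatment for cancer, which does not appear in any of the available databases", but treats this as a missing confounder and not as a gap in measuring the drugs under study.
- **Reassurance.** The Discussion does not expect information bias to matter much for the main variables, partly because "the pharmacological registry includes drugs dispensed in pharmacies (not only prescribed), and registry mortality is very reliable".
- **Safeguards.** Methods to Address Potential Sources of Bias sets a landmark (for example 3 months after diagnosis) and removes drugs prescribed in the 3 months before death. Statistical Analysis discards findings that also appear in the control cohort. The adjustment variables named there are age, sex and diagnostic groups.

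**The concern.** A patient who takes a chronic drug every day, at home and on the ward, collects fewer packs from the pharmacy during a period with admissions. If the ward supplies the drug, those days leave no dispensing record. Divided by calendar time, the recorded dose falls although the true dose has not changed.

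Hospital days in the months after a lethal cancer diagnosis are unlikely to be independent of prognosis. Where they are related to it, recorded dose carries prognostic information that has nothing to do with the drug. A graded relation between dose and survival is the kind of pattern that would promote a drug as a repurposing candidate. The screen runs over many drugs at P=.05, and Statistical Analysis applies no correction.

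The reason the Discussion gives for setting information bias aside, that pharmacy dispensing is captured, is where the gap lies. Dispensing records do not show what was taken during an admission.

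**Working it through.** **1. The plan's own figures.** The article gives none for this bias. Its one design calculation reproduces and is not in dispute: for 20% v 30%, two-sided 5%, power 80%, pooled proportion 0.25, n = [1.96 × √(2 × 0.25 × 0.75) + 0.842 × √(0.2 × 0.8 + 0.3 × 0.7)]² / 0.10² ≈ 293.2, so 294 per group. The 20% serves below as one baseline 5-year survival. The other, about 8%, follows from the example in Table 1: confidence / lift = 0.5000 / 6.4054 = 0.078.

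**2. The measurement error.** For a window of W days with H in hospital, if the ward supplies the drug and home stock is ignored:

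recorded average dose = true daily dose × (W − H) / W.

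With W = 90:

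| H (assumed) | Recorded / true dose |
|---|---|
| 3.0 | 87.0 / 90 = 0.967 |
| 7.7 | 82.3 / 90 = 0.914 |
| 13.5 | 76.5 / 90 = 0.850 |

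Dividing by (W − H) recovers the true dose.

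**3. Effect on an inert drug, landmark window.** Simulation with true dose independent of severity, comparing the top and bottom thirds of recorded dose. All inputs except baseline survival are assumptions: mean hospital days 3.0 to 13.5 in 90, mortality HR 1.5 to 2.7 per SD of severity, log-dose SD 0.1 to 0.6.

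- Whole range, calendar-day denominator: OR for 5-year survival 1.13 to 2.31; death rate ratio 0.94 to 0.64.
- Middle case (7.7 days, HR 2.0 per SD, log-dose SD 0.3, 20% survival): 16.4% v 22.6% alive at 5 years, OR 1.48, rate ratio 0.79. The chance of a significant protective result is 51% with 1000 users and 99% with 5000, against a nominal 2.5% in that direction.
- Middle case, but only half the hospital days reduce dispensing (home stock): OR 1.23.
- Hospital days unrelated to severity: OR 1.00.
- Out-of-hospital denominator: OR 0.98 to 1.02 in every scenario.

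**4. Average dose over survival time (the Machine Learning measure).** Assuming 10% to 30% of the last 6 months in hospital, 2% of earlier time, and log-dose SD 0.3: OR 1.27 to 2.32. Dropping the last 3 months before death leaves 1.17 to 1.85.

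**5. The safeguards.**

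- *Landmark.* It makes everyone alive at the cutoff. It does not equalise the days on which a pack could be collected before it.
- *Three-month exclusion.* For a patient who dies at month 8 it removes months 5 to 8; a month 0 to 3 window is untouched. For the survival-time dose it reduces the error without removing it (step 4).
- *Control cohort.* Assuming 0.3 to 1.0 hospital days per 90 in controls, the same mechanism gives OR 1.01 to 1.07, significant in 3% to 8% of analyses with 5000 users. The false finding would usually not be reproduced there, and so not discarded.
- *Adjustment.* Age, sex and diagnostic groups do not include hospital time.

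**6. Measures less affected.** For yes/no exposure among new starters, a separate inert-drug simulation with frailty-driven hospital days gave HR 0.93 to 0.96. The rule that removes patients who first use the drug after the cutoff should reduce this further, because a start delayed by admission is then usually excluded and not counted as unexposed. Maximum dose was not simulated; it involves no averaging over hospital days, so little effect is expected.

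**The case against.** **The text does not say that ward drugs go unrecorded.** Prescribing data and prescribed regimen are collected too, electronic prescription is deployed in public hospitals, and only hospital cancer treatment is declared missing. This stands as a limit: the gap is a strong inference, not stated fact. But the amount is still the quantity dispensed, and nothing says that the regimen will fill inpatient days.

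**Handling of inpatient days belongs in an analysis plan.** Partly right: Statistical Analysis fixes no denominator. But Machine Learning does fix one (survival time), and the Discussion makes a positive claim that information bias will matter little. Both are in the text.

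**The direction is not settled.** A reader might infer that the error always favours drugs. The documents do not support that. Early admissions include cancer surgery, which the study records with its date, and surgical patients may live longer. With 20% to 30% of patients having a 12-day surgical stay, a surgery HR of 0.3 to 0.4 and some non-adherence (all assumed), an inert drug gave HR 1.01 to 1.16 for 3 fills versus fewer: the false protection vanished or reversed. Higher dosing of sicker patients could also act the other way.

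**The size depends on the inputs.** This stands. With 4 to 7 hospital days, frailty HR 1.3 and modest non-adherence, the same comparison gave HR 0.89 to 0.92.

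**Adjusting every model for hospital days could hide real effects.** This stands. Those days can follow the start of the drug. For an effective drug acting through severity (assumed frailty HR 1.5, mean about 12 days), adjustment moved HR from 0.72 to 0.85 in one case and from 0.84 to 0.95 in another.

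**Everything is exploratory.** True, but a screen should not rank candidates on an artefact that a change of denominator can largely remove.

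**Conclusion.** The point holds for the dose measures averaged over time: average monthly dose, cumulative dose per unit of time, and average DDD over survival time. Read as calendar-time measures, they count inpatient days as zero-dose days, and no stated safeguard reliably removes the resulting error. The Discussion's reassurance is not justified for these variables.

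The size cannot be derived from the article. The range of OR 1.13 to 2.31 for an inert drug rests on assumed hospital days, on admissions marking worse prognosis, on the assumed spread of dose, and on dispensing stopping during admission. It shows that the error can matter, not how large it is in these data.

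Two stronger conclusions are tempting and unsupported. One is that all the drug analyses are compromised: yes/no exposure, which underlies the exposure odds ratio and the exposed-versus-unexposed survival comparison, is much less affected, as maximum dose should be. The other is that the bias must make drugs look protective: that depends on why patients are admitted, which the article does not describe.

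**What to change.** 1. Obtain admission and discharge dates from the linked hospital database (CMBD). Confirm first that they are available, since Outcome Variables and Measurements does not list them.
2. Compute average and cumulative dose per out-of-hospital day within the exposure window. Report this beside the calendar-time version, because home stock or packs collected during an admission could make it over-correct.
3. Adjust for hospital days in the window only as a sensitivity analysis, since those days may lie on the causal pathway.
4. In the Discussion, replace the statement that information bias will not materially affect the main variables with an acknowledgement of this gap for the dose variables.

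The cost is a small amount of extra data work and a slight loss of precision. Patients in hospital for the whole window have no measurable dose and drop out of the dose analyses; their number should be reported.

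### Having no recorded death is equated with being alive at 5 years, so deaths that the registry or linkage misses enter the long-survivor group, which the Discussion says is free of error

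*Protocol article*

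**What the plan says.** Four parts of the Protocol article bear on this.

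- **Statistical Analysis** sets the rule: "Patients who are censored, for whom no death is recorded during the follow-up time, are considered alive at the end of the period". The same section uses the resulting status in the first main comparison, in which "this exposure will be compared between patients considered alive at 5 years and those who have died using odds ratios". It uses survival time in the second: "A Cox regression model will be constructed to estimate the effect of the evaluated drug". The Machine Learning section uses 5-year survival as a yes/no outcome.
- **Outcome Variables and Measurements** runs survival from entry "until death or until 5 years of follow-up are reached". No other end of follow-up is named. The date of death comes from the INE cause-of-death registry.
- **Data Curation** states that "all patients without registration or enumeration in the death databases will be excluded".
- **Discussion** argues from the timing of database entry: "This allows all cases to be classified correctly in the group of patients identified as long survivors". It adds, without a figure, that "registry mortality is very reliable".

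**The concern.** The rule treats the absence of a death record as observed survival. For a patient who stayed linked and under coverage for 5 years, that is correct. For a patient who left coverage and then died without the death reaching the linked data, it is wrong. That patient joins the survivors in the odds ratio and the rule mining, and brings unobserved person-time into the Cox model.

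The leverage comes from rarity. Where 5% of patients survive, deaths outnumber survivors 19 to 1, so a small fraction of missed deaths is a much larger fraction of the survivor group. Rules in the Machine Learning section need only 5 patients, so one false survivor can be a fifth of the support for a rule.

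The Discussion considers only one error, true long survivors placed among the dead through late registration, and says that it biases toward the null. The rule above allows the opposite error, and that reassurance does not carry over to it. Under Methods to Address Potential Sources of Bias, the comparison group is limited to patients who never took the drug during their disease, and those who start after the cutoff are removed. A patient who leaves coverage produces no later dispensing records and so stays a never-user with 5 years of credited survival. A patient who remains observed and starts the drug later is dropped. The error can therefore differ by exposure.

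**Working it through.** **The plan's own figure.** Sample Size Considerations gives 294 per group for 20% against 30%, taken as two-sided 5% with 80% power. With the pooled-variance formula:

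n = [1.96·√(2·0.25·0.75) + 0.8416·√(0.2·0.8 + 0.3·0.7)]² / 0.10² = (1.2002 + 0.5119)² / 0.01 ≈ 293.1, rounded up to 294.

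It reproduces, and this point does not challenge it.

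**Inputs.** True 5-year survival S comes from Table 2: metastatic bladder 5%, pancreas 8.2%, lung 18.1%. The stated maximum is 20%. The 5-year probability of leaving observation, l, is not in the documents; 0.5% to 2% is assumed. Both models below assume that every death after leaving is missed.

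**Model A, all loss at diagnosis (upper bound).** False survivors F = l(1−S). Their share of apparent survivors is F/(F+S). For S = 5% and l = 2%: 0.019/(0.019 + 0.05) = 27.5%.

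**Model B, loss accruing at a constant rate.** Let λ = −ln(S)/5 be the death hazard and γ = −ln(1−l)/5 the loss hazard, independent of each other. False survivors are those who leave first and then die before year 5:

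F = (1−S) − [λ/(λ+γ)]·[1 − e^(−5(λ+γ))].

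For S = 5% and l = 2%: λ = 0.5991, γ = 0.00404, F = 0.00537, share = 0.00537/0.05537 = 9.7%. The share is smaller because in lethal cancers most patients die, and are recorded, before they can leave. Deaths missed are then 0.00537/0.95 = 0.57%, against 2% in Model A.

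| S | Model B, l = 0.5% to 2% | Model A, l = 0.5% to 2% |
|---|---|---|
| 5% | 2.6% to 9.7% | 8.7% to 27.5% |
| 8.2% | 1.7% to 6.5% | 5.3% to 18.3% |
| 18.1% | 0.8% to 3.2% | 2.2% to 8.3% |
| 20% | 0.7% to 2.9% | 2.0% to 7.4% |

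**Effect if the error is unrelated to exposure.** Under Model A with l = 2%, 20% against 30% becomes 0.20 + 0.02·0.80 = 21.6% against 0.30 + 0.02·0.70 = 31.4%. The odds ratio falls from 1.71 to 1.66, and power at 294 per group falls from 80.1% to 76.9%. This is a small dilution.

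**Effect if the error differs by exposure.** Take a true odds ratio of 1 and, as an extreme, missed deaths only among the unexposed. The observed odds ratio is [S/(1−S)] / [(S+F)/(1−S−F)]. At l = 2%:

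| S | Model B | Model A |
|---|---|---|
| 5% | 0.90 | 0.71 |
| 20% | 0.96 | 0.91 |

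A null drug then looks harmful. Loss concentrated among the exposed would shift the result the other way.

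**The passages side by side.** Data Curation, read literally, removes anyone with no entry in the death databases. Statistical Analysis counts those same people as alive. The literal reading would leave no survivors, so the exclusion presumably means patients who cannot be linked. On that reading the two sections agree, but a patient who was linked and later left coverage is still not identified.

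**The case against.** The strongest defence is that survival here is not tracked through clinic attendance. Deaths come from a national registry built on death certificates and judicial bulletins, and the Discussion calls it very reliable. A reader might infer that everyone lost to follow-up becomes a false survivor. The documents do not support that: a patient who stops attending but whose death is registered and linked is still counted as dead. Only missed deaths contaminate the group. This stands and narrows the point.

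A reader might also infer that Data Curation and Statistical Analysis flatly contradict each other. That holds only on a literal reading that cannot be intended. On the sensible reading, the exclusion already removes unlinkable patients, which helps the plan. What is left there is a fault of wording.

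It would also be tempting to quote 9% to 27% as the expected size. That range puts all loss at diagnosis and is an upper bound under the assumed rates. With accrual over time the figures are about a third of that. Nor is the survivor group small in number: Table 2 expects 283 to 4259 per cancer. It is small only as a share.

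Finally, exposure is fixed at a landmark among patients alive at that date, so leaving afterwards does not erase exposed status. That removes much of the scope for differential error. The never-user condition over the whole disease course keeps some of it.

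The study is declared exploratory, which lowers the stakes. It does not make the Discussion's statement about long survivors correct.

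**Conclusion.** The concern holds in a limited form. The stated rule credits 5 years of survival to any patient whose death is missed, and no end of follow-up for loss of coverage is defined. The status feeds the odds ratio, the Cox model and the rule mining. For most patients without a death record the rule gives the right answer.

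Under an assumed 5-year loss of 0.5% to 2%, with all deaths after leaving missed, false survivors are about 3% to 10% of the long-survivor group at 5% survival with accruing loss, and up to 9% to 27% if all loss is at diagnosis. At 18% to 20% survival they are about 1% to 3%, and up to 2% to 8%. The true rate is unknown and may be lower. If the error is unrelated to exposure, its effect is small. If it differs by exposure, it can move an odds ratio in either direction. The Discussion's claim of error-free long survivors, and its reassurance about bias toward the null, therefore need qualifying. The point does not overturn the design or the sample size.

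**What to change.** 1. End follow-up at the earliest of death, 5 years, or end of health-system registration where that date can be obtained, and censor the Cox model there.
2. Keep the present rule for the main odds ratio. Add a sensitivity analysis that leaves out apparent survivors with no evidence of life or registration late in follow-up. That evidence should not come from dispensing, because survivor status would then depend on the exposure. Report the number of unconfirmed patients by exposure.
3. Reword Data Curation so that it excludes patients who cannot be linked to the death registry, not everyone without a death entry.
4. Qualify the Discussion: long survivors are correctly classified with respect to late registration, but missed deaths are possible and their direction of bias is not fixed.

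The cost is a little more programming and a query to the data provider, since the documents do not say that coverage dates were supplied. The sensitivity analysis favours survivors who use care, and they are plausibly more medicated. For that reason it should stand beside the main analysis and not replace it, and a contact at or after year 5 should not become the primary definition of survival.
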